## Introduction 

Surgery is a highly prevalent primary treatment for localized tumors. Patients undergoing cancer surgery are at risk for surgery-related morbidity and mortality. For example, the rates of mortality and significant complications within 30 days of major abdominal cancer surgery are 4 and 50%, respectively (1). Numerous health-related quality of life (HRQOL) consequences are also common after oncologic surgery and may persist for an indefinite period (2). Frail cancer patients are especially at risk for surgery-related complications that lead to morbidity and mortality. Rockwood et al. define frailty as a multidimensional syndrome of diminished reserves that lead to increased vulnerability (3). A meta-analysis assessing the relationship between frailty and adverse outcomes across all surgical procedures found that frailty was associated with increased risk of surgical and perioperative complications, as well as readmission, postoperative discharge to skilled care, and mortality (4). Many of these adverse surgical outcomes have shown to be related to prolonged pain (5) and functional disability (6–9), as well as greater healthcare costs (10–12). Accordingly, identifying and mitigating frailty in cancer patients and other at-risk groups (*e.g.*, geriatric) are recommended to appropriately manage surgical risk (13, 14).

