### Sample Size

A period of trial enrolment, rather than target sample size, was selected to inform expected rates of referral for a clinical service. The trial anticipates receiving 150 referrals for prehabilitation over 12 months. We estimate that one third of all referred patients will decline the intervention but will consent to making their hospital records related to their pending cancer surgery available for research (hereafter referred to as ‘usual care’ participants).

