### Study Outcomes

Participant data to assess feasibility and derive estimates of effect are collected from the participants’ referrals, at the baseline assessment, within 1 week prior to surgery, and at 30 and 90 days postoperatively.

The total number of referrals and the rate at which they are received (per month) will be reported. To characterize the patients referred to the program, the following are collected from all referral forms (including usual care participants and those who decline research): referring surgical service; reason for referral; frailty level (*via* the Clinical Frailty Scale (3), embedded into the referral); cancer type; indicated surgery; referring healthcare practitioner type (*i.e.* physician, surgeon, clinic nurse, *etc.*), and participant demographics (age, sex, and general geographic location). The enrolment rate will be calculated as [# of enrolled participants]/[# of referred participants]. The frequency and reasons for declining participation in the study, declining prehabilitation (*i.e.*, usual care participants), and drop-out will be reported and compared using descriptive statistics of demographic and referral data.

Given the importance of scheduling and timing for prehabilitation relative to the date of surgery, several relevant time periods will be reported. The time from program referral to the date of surgery will be reported and is referred to as the ‘prehabilitation window’. We will also report the total preoperative period (time between consent for surgery and date of surgery) and prehabilitation duration (time from baseline assessment to surgery).

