Reporting of the exercise prescription parameters and adherence to the programming will follow the Consensus on Exercise Reporting Template (62). Adherence to home and facility-based exercise sessions are recorded *via* attendance and standardized logbooks capturing training activity completed by the research coordinator. Adherence to stress management, nutrition plan, protein consumption, and utilization of smoking cessation tools (as required) is recorded weekly using a logbook within the participant manuals. Healthy eating practices advised by the dietitian are also assessed by a 3-day diet record in the week prior to surgery. Safety or adverse events related to prehabilitation are discussed during weekly communication between the participants and the research coordinator. Reporting and grading of adverse events will follow the Common Terminology Criteria for Adverse Events version 5.0 (63).

Estimates of program effectiveness are derived from a combination of patient-reported and functional performance measures, as well as clinical information from the medical record at each of the study timepoints. Aerobic functional capacity is measured using the Six-Minute Walk Test (6MWT) (64) and musculoskeletal functional capacity is assessed *via* grip strength using an isometric dynamometry (Jamar, Sammons Preston, Bolingbrook, IL, U.S.A.) according to established protocols (44). Body mass (kilograms) and height (meters) are measured using standardized procedures and are used to calculate body mass index (BMI, kg/m^2^). Body fat percentage, fat and fat free mass, impedance, resistance, and phase angle are recorded are measured *via* bioelectrical impedance analysis (mBCA 514, Seca, Hamburg, Germany) (65). HRQOL is measured using the 12-item Short Form Health Survey (SF-12) (66, 67) and the EuroQol 5 Dimensions 5 Levels (EQ5D-5L) (68) The Patient Health Questionnaire (PHQ-9) is used to assess depression (69). The EFS, PSS, and GLTEQ are also re-administered at each follow-up timepoint. Postoperative length of stay in number of days (including any readmissions) is recorded from the medical record. Complications, including mortality, are reported according to the Clavien-Dindo classification (70). All health events that require readmission will also be documented. Complication and health event data are extracted from the medical record at the 30^th^ and 90^th^ postoperative day for each participant.

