### Analytic Plan

The analytic plan is described for prehabilitation implementation feasibility outcomes and exploratory analyses of prehabilitation effects. In line with comparative effectiveness research, presentation of confidence intervals will be emphasized for the purpose of accurately reflecting the actual data as well as directly addressing the uncertainty of the data. All quantitative analyses will be conducted in R (R Foundation for Statistical Computing, Vienna, Austria) and an alpha of.05 will be used.

Demographic and disease characteristics of all referred patients, as well as prehabilitation and usual care participants**’** will be summarized with appropriate parametric and non-parametric statistics. Reasons for ineligibility, declined participation in the study or intervention, as well as reasons for choosing FBP or HBP will be tallied. Group comparisons for referral information (surgical service, type of cancer, type of surgery, age, sex, and geographic location) will be assessed by one-way analysis of variance (ANOVA) for continuous and Chi-square test for categorical variables and described across FBP, HBP, usual care, and participants who decline participation. Baseline demographic and disease-related variables will be compared between study participants (FBP, HBP and usual care) ***via*** one-way ANOVA for continuous variables and Chi-square test for categorical variables.

Adherence to the interventions will be summarized dichotomously as meeting or not meeting the prescribed intervention components across each domain (exercise, nutrition, psychology, and smoking cessation). Reasons for deviations will be thematically categorized and summarized by frequency and percentage. Retention rates will be calculated as a total percentage of dropouts at the presurgical time point to the total participants enrolled for FBP and HBP. Reasons for dropout will be summarized using frequencies and percentage for each prehabilitation arm. Reported safety or adverse events will be summarized using frequencies and percentage for each group.

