To provide an estimate of effect of HBP and FBP, point estimates and 95% confidence intervals will be calculated for changes in physical fitness, patient-reported outcomes from baseline to the 90-day time point using linear mixed effect models. Estimated mean hospital length of stay for HBP, FBP, and usual care, as well as between-group differences, will also be conducted using a linear mixed effect model. Incidence rate ratios and estimating rate differences for postoperative complication, readmission, and morbidity for prehabilitation in reference to usual care at 30 and 90 days after surgery will be made using Poisson regression. Tukey HSD will be used to adjust for multiple comparisons. In the presence of outliers, bootstrapping regression coefficient methodology will be done to obtain valid confidence intervals.

Semi-structured interviews regarding participant satisfaction as well as facilitators and barriers with the intervention will be transcribed verbatim and undergo qualitative content analysis. Initial transcript sample readings will be independently done by two researchers. Preliminary themes will be noted, and differences will be resolved, and duplications will be eliminated. Themes and content will be analyzed descriptively. Coding, linking, and retrieving the qualitative data will be conducted using NVivo software (QSR International, Melbourne, AUS).

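### If complications cause missed day 30 and day 90 assessments, mixed models without complication status would overstate recovery; chart data already collected can guard against this

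*Protocol article*

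**What the plan says.** Study Outcomes places the measurements "at the baseline assessment, within 1 week prior to surgery, and at 30 and 90 days postoperatively". For fitness and patient-reported outcomes, the Analytic Plan gives point estimates and 95% confidence intervals for "changes in physical fitness, patient-reported outcomes from baseline to the 90-day time point using linear mixed effect models". It lists no covariates, auxiliary variables or missing-data assumption for these models.

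Study Outcomes also states that "Complication and health event data are extracted from the medical record" at postoperative days 30 and 90 for every participant, so this information does not depend on attending an assessment. In the Analytic Plan, complications and readmissions appear only as outcomes of a separate Poisson regression: "Incidence rate ratios and estimating rate differences for postoperative complication, readmission, and morbidity for prehabilitation in reference to usual care".

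Completeness after surgery is not among the stated summaries: "Retention rates will be calculated as a total percentage of dropouts at the presurgical time point". Usual care participants contribute hospital records only (Sample Size), so the fitness and questionnaire estimates are changes within the home-based and facility-based arms.

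**The concern.** A likelihood-based mixed model handles missed visits without bias when missingness depends only on data in the model. A complication occurs after the last preoperative measurement. If it keeps a patient from the day 30 walk test and would also have lowered the result, the two preoperative values hold little or no record of it. The model then fills the gap from patients who did attend, and fewer of those had complications.

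The estimates at stake answer RQ2a in Box 1, on change up to 90 days after surgery. There is no usual care series on these outcomes against which an optimistic drift would show. The Analytic Plan gives confidence intervals prominence as its expression of uncertainty, but an interval does not reveal this kind of bias.

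**Working it through.** The article has no postoperative missing rate and no power calculation, so there is no plan figure to reproduce.

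**Inputs from the article**
- "The trial anticipates receiving 150 referrals for prehabilitation over 12 months", and "one third of all referred patients will decline the intervention but will consent to making their hospital records" (Sample Size): 150/3 = 50 usual care, leaving at most 150 - 50 = 100 for the two prehabilitation arms.
- "the rates of mortality and significant complications within 30 days of major abdominal cancer surgery are 4 and 50%, respectively" (Introduction). This is a background figure for one type of surgery, not a trial assumption.

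**Assumed inputs (not in the documents)**
- Complication risk *p*: 30-50%.
- Loss in six-minute walk distance after a complication, *d*: 40-80 m at day 30, 20-40 m at day 90.
- Share missed: *mc* = 50-60% of complicated patients, *mu* = 15-20% of others.
- SD 90 m, correlation between visits 0.75, 50 enrolled per arm, 65% seen.

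**Step 1: closed form.** If missingness depends only on complication status and preoperative values are unrelated to it, a model without that status targets the mix of patients who attend:
- *p_obs* = *p*(1 - *mc*) / [*p*(1 - *mc*) + (1 - *p*)(1 - *mu*)]
- bias = *d* × (*p* - *p_obs*)

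Day 30, low end (*p* = 0.3, *d* = 40 m, 50%/15% missed): *p_obs* = 0.150/(0.150 + 0.595) = 0.2013; bias = 40 × 0.0987 = 3.9 m.

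Day 30, high end (*p* = 0.5, *d* = 80 m, 60%/15% missed): *p_obs* = 0.200/(0.200 + 0.425) = 0.32; bias = 80 × 0.18 = 14.4 m.

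**Step 2: simulation.** Maximum likelihood for four visits, 60,000 patients, five scenarios within the assumed ranges:

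| Scenario | Day 30 bias (m) | Day 90 bias (m) |
|---|---|---|
| 1 | 6.5 | 2.1 |
| 2 | 4.3 | 1.6 |
| 3 | 9.7 | 3.6 |
| 4 | 4.9 | 1.8 |
| 5 | 13.6 | 4.7 |

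Day 90 is smaller because the assumed loss is halved and because a day 30 value, where seen, recovers part of it. If the same patients missed both visits, the closed form at the high end gives 40 × 0.18 = 7.2 m at day 90.

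**Step 3: standard error of an arm's mean change.** SD of change = 90 × √(2 × (1 - 0.75)) = 63.6 m. Number seen = 50 × 0.65 = 32.5. SE = 63.6/√32.5 = 11.2 m.
- Day 30: 4.3/11.2 to 13.6/11.2 = about 0.4 to 1.2 SE.
- Day 90: 1.6/11.2 to 4.7/11.2 = about 0.14 to 0.42 SE (7.2/11.2 = 0.64 at the ceiling above).

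**Step 4: check in SD units, which applies to any outcome.** This is a separate fit with correlation 0.6, the same loss at both postoperative visits, and both visits missed together. The SE for 100 patients is about 0.09-0.10 SD.

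| *p* | *d* (SD) | Missed, complicated/other | Day 90 bias (SD) |
|---|---|---|---|
| 0.5 | 0.5 | 10%/10% | 0.000 |
| 0.2 | 0.5 | 40%/10% | 0.025 |
| 0.5 | 0.5 | 40%/10% | 0.046 |
| 0.5 | 0.8 | 60%/10% | 0.154 |

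The range runs from no bias to about 1.5 SE (0.154/0.103). With equal missing rates *p_obs* = *p*, so the bias vanishes.

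**Step 5: with complication status used.** The residual is at most 0.4 m in the Step 2 scenarios, and between -0.004 and +0.001 SD in the separate fit. Both simulations let missingness depend on complication status alone, so this shows that the method works under that assumption. It is not evidence that the assumption holds.

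**The case against.** The strongest reply is that this rests on silence. The article names a class of model, and an article commonly leaves covariates, auxiliary variables and imputation to a fuller plan, which is not shown here. That stands: the silence is not itself an error, and nothing in the article rules out the analysis proposed below.

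Three stronger readings are tempting, and the documents do not support them:
- *The models use only the outcome series.* A reader might infer this because complications appear only as Poisson outcomes, but the article does not say it.
- *Patients who miss visits are treated as uncomplicated.* They are predicted from all who attend. At the high end of Step 1, 32% of attendees still had a complication.
- *Recovery is overstated.* This holds only if missing rates differ by complication status. The article gives no such rates, and its 50% complication figure is for major abdominal surgery, whereas the trial also takes breast, urological, and head and neck cases.

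Other parts of the reply also have force. Preoperative fitness and frailty scores may carry some information on complication risk, since the Introduction links frailty to complications. Under Box 2, contact is by telephone or web and questionnaires continue, so the missed-visit mechanism is probably weaker for patient-reported outcomes. Some fitness data are absent because of pandemic restrictions, which is unrelated to complications. The analyses are exploratory, and the Discussion already concedes that precision will be limited.

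What remains is that the information needed to protect the named estimator is held on every participant, and the stated analysis gives it no role there.

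**Conclusion.** The point holds in conditional form. If complications lead to missed assessments and the mixed models leave out complication status, change in fitness and patient-reported outcomes after surgery will look better than it was. Under the assumed inputs the overstatement in six-minute walk distance is about 4-14 m at day 30 (0.4 to 1.2 SE). At day 90, the end point the Analytic Plan names, it is about 2-5 m (0.14 to 0.42 SE), and somewhat more if the same patients miss both visits. It is zero if missing rates are equal.

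The direction follows from the mechanism, while the size depends on missing rates, losses and variability that the documents do not give. This is an inexpensive improvement to exploratory secondary estimates (RQ2a), not a demonstrated error, and it does not touch the feasibility objective.

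**What to change.** - Keep the linear mixed model, but fit it after multiple imputation of missed day 30 and day 90 outcomes among participants alive at that time. Use chart-recorded Clavien-Dindo grade, readmission and length of stay as auxiliary variables in the imputation model.
- Do not impute in-person outcomes omitted by design under Box 2 item 7.
- Report the completeness of day 30 and day 90 assessments by complication status, so that readers can see whether the condition for bias is met.
- Show the unimputed mixed model alongside as a sensitivity analysis.

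If a fuller analysis plan already does this, a sentence in the Analytic Plan is enough. Otherwise the cost is plan wording and programming, slightly wider intervals, and an imputation model to document. With about 32 patients per arm observed under the assumptions above, that model should stay small. It still assumes that, given the recorded events, missingness does not depend on the unseen outcome.

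### Length of stay is one value per patient, but the plan assigns it a linear mixed model without naming a grouping factor, so the model as written cannot be fitted as a mixed model

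*Protocol article*

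**What the plan says.** Protocol article, Study Outcomes, defines the outcome: "Postoperative length of stay in number of days (including any readmissions) is recorded from the medical record". That is one total per patient; no repeated measure of stay is described.

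The Analytic Plan first assigns linear mixed models to the repeated fitness and patient-reported outcomes. It then turns to stay. The target is "Estimated mean hospital length of stay for HBP, FBP, and usual care". The method is given later in the same sentence: "as well as between-group differences, will also be conducted using a linear mixed effect model". It names no random effect, grouping factor or covariate for this model. It adds "Tukey HSD will be used to adjust for multiple comparisons" and "In the presence of outliers, bootstrapping regression coefficient methodology will be done to obtain valid confidence intervals", without saying what counts as an outlier. All quantitative analysis is to be done in R.

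On numbers, the Sample Size section says "The trial anticipates receiving 150 referrals for prehabilitation over 12 months" and "We estimate that one third of all referred patients will decline the intervention".

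**The concern.** A mixed model needs at least some groups that contribute more than one record. The fitness and questionnaire data have them, because each patient is measured repeatedly. Stay does not. Applying the same model to stay, which is how the word also in that sentence reads, asks for a patient variance that the data cannot supply.

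Once the random effect drops out, what remains is a linear model with a single residual variance. That is a doubtful description of a non-negative count of days pooled over operations from lumpectomy to lung resection (Table 2), where spread is likely to grow with the mean.

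Two uses depend on the result. The Analytic Plan says that confidence intervals will be emphasised. The economic section multiplies the difference in stay between programme and usual care patients by the unit cost of an inpatient day. The comparison is also non-randomised, so a model without covariates leaves differences in case mix in the estimate.

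**Working it through.** The protocol gives no mean, standard deviation or coverage figure for stay, so it has no figure of its own to reproduce.

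**Inputs from the protocol.** 150 expected referrals; one third to usual care, 150 / 3 = 50, leaving at most 100 in the two programme arms together; three groups; 95% intervals; R.

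**Assumed inputs.** Lognormal or gamma stay, means of 5 to 8 days, standard deviation proportional to the mean, and the split between home and facility arms.

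**1. Is the patient effect identifiable?** With one row per patient the covariance matrix is (τ² + σ²)·I, where τ² is the patient variance and σ² the residual variance. Only the sum enters the likelihood. On simulated data with 50 per group, the REML log-likelihood was −346.155 whether τ² was 0, 25, 50, 75 or 99% of the total. The standard error of a group contrast is √[(τ² + σ²)(1/50 + 1/50)] = √(37.704 × 0.04) = 1.228 at every split.

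**2. What does R do?** On a second simulated set:
- lme4::lmer stops, because the number of grouping levels must be smaller than the number of observations.
- nlme::lme returns an arbitrary split, 41.896 + 5.892 = 47.787. The contrast has standard error √(47.787 × 0.04) = 1.383.
- lm gives the same estimate (−0.82 for home versus facility) and the same standard error (1.383).

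So the interval from the mixed model, where it fits, is the interval from ordinary regression. A random effect for an assumed 8-level surgical service could be estimated, but the protocol does not name one.

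**3. How does the constant-variance interval behave?** Take 100 versus 50 patients with a coefficient of variation of 1. The pooled variance is (99·s₁² + 49·s₂²)/148. The variance that the model assigns to the difference is that value × (1/100 + 1/50), and the true variance is s₁²/100 + s₂²/50. Approximate coverage is 2Φ(1.976 × SE ratio) − 1. The ratio does not depend on the coefficient of variation.

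| True means | Model variance | True variance | SE ratio | Approx. coverage | Simulated (20,000 runs, CV 0.8–1.2) |
|---|---|---|---|---|---|
| 7 vs 7 | 49.00 × 0.03 = 1.470 | 1.470 | 1.000 | 0.952 | 0.953–0.955 |
| 6 vs 8 | 45.27 × 0.03 = 1.358 | 1.640 | 0.910 | 0.928 | 0.922–0.929 |
| 5 vs 8 | 37.91 × 0.03 = 1.137 | 1.530 | 0.862 | 0.912 | 0.906–0.909 |

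The shortfall comes from unequal variance combined with unequal group size. Skew alone does not produce it.

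**4. Three groups, as planned.** With 50/50/50 and means 5/5/7, the residual variance is (25 + 25 + 49)/3 = 33, so each contrast is given 33 × 0.04 = 1.32.
- Contrasts with usual care have true variance (25 + 49)/50 = 1.48, giving coverage of about 0.938 (simulated 0.934–0.942).
- Home versus facility has true variance 50/50 = 1.00, giving about 0.977 (simulated about 0.974), which is too wide.
- Tukey simultaneous coverage was 0.947–0.953.
- In the most unbalanced split tried (60/15/25), the lowest single contrast was 0.909 and Tukey coverage was 0.936–0.938.

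**5. Does the bootstrap help?** In two-group runs (2,000 each, Monte Carlo error about 0.006), percentile bootstrap intervals covered 0.902–0.943 and pooled intervals 0.910–0.961. In the 50 versus 100 setting with means 7 and 5, pooled was 0.919, bootstrap 0.916 and Welch 0.930.

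**6. Does robust variance help?** At 100 versus 50 with unequal means, a log-link model with robust variance covered 0.934–0.943, against 0.906–0.929 for the pooled interval. With equal means it covered 0.934–0.947, slightly below the pooled interval. The gain is real but partial.

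**The case against.** The best reply is that the protocol never says the random effect is for the patient. Surgical service is collected and could be the cluster, and such detail is often left to a statistical analysis plan. Clinical information is also drawn from the record at each study timepoint, and the economic section separates index stay from readmission stay, so more than one record per patient is conceivable. The plan also provides Tukey adjustment and a bootstrap, effectiveness is exploratory, and the Discussion concedes limited power.

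Part of this stands. A service-level effect would be estimable, the exploratory status limits the severity, and Tukey coverage is close to nominal when the groups are balanced. It does not remove the point. The outcome is defined as a single total that includes readmissions, and the 30- and 90-day timing is attached to complications and health events. The model class is stated for an outcome that cannot support it unless the plan names something it does not name.

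A reader might infer three stronger things, none of which the documents support:
- **That the unidentified random effect makes the intervals too narrow.** It does not; the standard errors equal those of ordinary regression.
- **That the intervals will under-cover as a matter of fact.** That depends on an assumed difference in means with proportional spread; with equal means coverage is about 95%.
- **That the linear model wastes power.** Analysing log days targets geometric means, whereas the plan and its cost calculation need arithmetic mean days. A gamma log-link model with group terms only reproduces the raw group means, so it promises no gain in efficiency by itself.

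**Conclusion.** The point holds as a mismatch between the stated model and the recorded data. A patient random effect for length of stay is not identifiable and no other grouping factor is given. As written, the analysis either fails in R or becomes a constant-variance linear regression without covariates.

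The effect on the intervals is conditional and modest. Coverage is about 95% with equal means and about 91 to 93% at 100 versus 50 with differences of 2 to 3 days and spread proportional to the mean; some contrasts are too wide instead. The lognormal shape, the means and the group split are assumptions, because the protocol gives none. The conditional bootstrap does not reliably improve matters, and its undefined trigger lets the interval method be chosen after the data are seen.

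Severity is low to moderate: the analysis is exploratory, but it feeds the hospital cost impact.

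**What to change.** - Keep linear mixed models for the repeated fitness and questionnaire outcomes.
- For stay, specify a one-record-per-patient model for mean days (linear, or a log-link generalised linear model) with heteroscedasticity-robust variance. If a cluster such as surgical service is intended, name it.
- Adjust for surgery type, age and Clinical Frailty Scale, all of which are on the referral form for programme and usual care patients alike.
- Report the adjusted difference in mean days with its 95% confidence interval. This is the quantity that the inpatient-day costing uses.
- State the interval method in advance. If a bootstrap is wanted, use it for every analysis of stay, not only after a search for outliers.

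The cost is a change of analysis wording. No new data are needed. Robust intervals can still fall slightly short of 95% at these sample sizes, and the write-up should say so.

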**Methods:**

This is a pilot pragmatic clinical trial conducted in a large academic hospital in Toronto, Ontario, Canada to assess feasibility of clinical implementation and derive estimates of effectiveness. Feasibility data include program referral rates, enrolment and attrition, intervention adherence and safety, participant satisfaction, and barriers and facilitators to programming. The study aims to receive 150 eligible referrals for adult, English-speaking, preoperative oncology patients with an identified indication for prehabilitation (*e.g*., frailty, deconditioning, malnutrition, psychological distress). Study participants undergo a baseline assessment and shared-decision making regarding the intervention setting: either facility-based prehabilitation or home-based prehabilitation. In both scenarios, participants receive an individualized exercise prescription, stress-reduction psychological support, nutrition counseling, and protein supplementation, and if appropriate, smoking cessation program referrals. Secondary objectives include estimating intervention effects at the week prior to surgery and 30 and 90 days postoperatively. Outcomes include surgical complications, postoperative length of stay, mortality, hospital readmissions, physical fitness, psychological well-being, and quality of life. Data from participants who decline the intervention but consent for research-related access to health records will serve as comparators. The COVID-19 pandemic required the introduction of a ‘virtual program’ using only telephone or internet-based communication for screening, assessments, or intervention was introduced.

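### Poisson intervals for the event outcomes are safeguarded only against outliers, and the model list names an undefined morbidity outcome where mortality was declared

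*Protocol article*

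**What the plan says.** The Analytic Plan covers "Incidence rate ratios and estimating rate differences for postoperative complication, readmission, and morbidity", and the sentence continues "for prehabilitation in reference to usual care at 30 and 90 days after surgery will be made using Poisson regression". It names no variance estimator and does not mention dispersion. The one rule on interval validity is "In the presence of outliers, bootstrapping regression coefficient methodology will be done to obtain valid confidence intervals". The same section says that "presentation of confidence intervals will be emphasized", so intervals are the main inferential output.

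Two other places define the outcomes. The Methods part of the abstract states: "Outcomes include surgical complications, postoperative length of stay, mortality, hospital readmissions, physical fitness, psychological well-being, and quality of life". Mortality is a separate item there, and morbidity is not in the list. Study Outcomes says "Complications, including mortality, are reported according to the Clavien-Dindo classification", and on readmission: "All health events that require readmission will also be documented". Neither statement settles whether the analysis variable is one indicator per patient or a number of events per patient.

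**The concern.** A Poisson model takes the variance of the outcome to equal its mean. An indicator with risk p has variance p(1-p), which is smaller, so model-based Poisson intervals are too wide. When events are counted, one patient may have several linked complications or repeat readmissions. The variance may then exceed the mean, and the same intervals become too narrow. The article leaves the outcome type open, so the direction of the error cannot be read from it.

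The outlier-triggered bootstrap does not close this gap. A yes/no variable has no outliers in the usual sense, and counts can be overdispersed without any single extreme value. Resampling patients could give sound intervals, but the condition attached to it means it might never be used where it is needed.

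The outcome list is a second problem. Morbidity is not defined apart from complications, so the list appears to name one construct twice and leave out a declared one. At stake is the comparison with usual care on clinical events (research question 2b), where a reader will judge the plausible range of effect from these intervals.

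**Working it through.** The article gives no power calculation or interval width for these outcomes, so there is no planned figure to reproduce.

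**Inputs from the article**
- Sample Size: 150 referrals, a third of them expected as usual care. 150/3 = 50 usual care, and 150 - 50 = 100 prehabilitation. Both are upper limits, since some of those referred will decline research.
- Introduction: "the rates of mortality and significant complications within 30 days of major abdominal cancer surgery are 4 and 50%, respectively".
- Introduction: one cited randomized trial in high-risk patients roughly halved complications, giving 50% versus 25% as an illustration.

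**Assumed, because the article gives no figure:** event rates of 10% and 15%; variance-to-mean ratios (phi) of 1.25, 1.5, 2 and 3.

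**Yes/no outcomes.** Standard error (SE) of the log ratio, with n1 = 100 and n0 = 50:
- Poisson model-based: sqrt[1/(n1 p1) + 1/(n0 p0)]
- Correct for indicators: sqrt[(1-p1)/(n1 p1) + (1-p0)/(n0 p0)]

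At 50% in both groups these are sqrt(1/50 + 1/25) = 0.245 and sqrt(0.5/50 + 0.5/25) = 0.173. Their ratio is 1.41. With equal risks the ratio is 1/sqrt(1-p), whatever the group sizes. Actual coverage of a nominal 95% interval is 2*Phi(1.96 x ratio) - 1.

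| Usual care vs prehabilitation | SE, Poisson | SE, correct | Ratio | Interval, Poisson | Interval, correct | Coverage, Poisson |
|---|---|---|---|---|---|---|
| 50% vs 50% | 0.245 | 0.173 | 1.41 | 0.62-1.62 | 0.71-1.40 | 99.4% |
| 50% vs 25% | 0.283 | 0.224 | 1.26 | 0.29-0.87 | 0.32-0.78 | 98.7% |
| 15% vs 15% (assumed) | 0.447 | 0.412 | 1.08 | 0.42-2.40 | 0.45-2.24 | 96.7% |
| 10% vs 10% (assumed) | 0.548 | 0.520 | 1.05 | 0.34-2.93 | 0.36-2.77 | 96.1% |
| 4% vs 4% | 0.866 | 0.849 | 1.02 | 0.18-5.46 | 0.19-5.28 | 95.5% |

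**Counts.** With variance phi times the mean, coverage is 2*Phi(1.96/sqrt(phi)) - 1. This gives 92.0% at phi = 1.25, 89.0% at 1.5, 83.4% at 2 and 74.2% at 3. At phi = 1 the plain Poisson interval is correct.

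**Simulation check** (3,000 simulated trials per scenario; Poisson fit with model-based and with robust sandwich variance; counts with mean 1):

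| Scenario | Model-based coverage | Robust coverage |
|---|---|---|
| Yes/no, 50% vs 50% | 99.2% | 95.2% |
| Yes/no, 50% vs 25% | 99.0% | 95.7% |
| Yes/no, 15% vs 15% | 97.3% | 96.0% |
| Counts, phi = 1.5 | 88.5% | 94.1% |
| Counts, phi = 2 | 83.7% | 94.0% |
| Counts, phi = 3 | 75.2% | 93.7% |

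**Mortality.** Applying 4% to all 150 referrals gives 0.04 x 150 = 6 deaths at most. The chance of no deaths in at least one group is 0.96^50 + 0.96^100 - 0.96^150 = 0.130 + 0.017 - 0.002, or about 14%. A Poisson ratio then has no usable estimate. This agrees with the simulation, where only 2,560 of 3,000 runs had a death in both groups. At this rate the problem is sparse data rather than the variance formula.

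**The case against.** The strongest objection is that the article is silent on the variance estimator. It names a model and does not say that model-based variance will be used. Poisson regression with robust variance is still Poisson regression, and an analysis plan that is not shown may specify it. This stands in part: a reader might infer that the plan commits to plain Poisson intervals, and the text does not support that. What remains is that the article does state a rule for obtaining valid intervals, and its trigger fits neither source of error.

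A reader might also infer that every event interval will be wrong. That does not follow. The two errors are alternatives that depend on the outcome type. The rate wording and the recording of all readmission events lean towards counts, where error arises only with overdispersion, and the article gives no dispersion figure. For yes/no outcomes the excess is small at low rates and errs on the conservative side. The 50% rate is for major abdominal surgery, while the trial also takes breast, urological and head and neck surgery.

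Nor is it an error to promise rate differences from a Poisson model. No log link is specified, and differences can come from an identity link or from model predictions.

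On mortality, deaths are counted within Clavien-Dindo complications, so they are not lost, and morbidity is probably a slip of wording. That softens the gap but does not close it, because a death counted as a complication yields no mortality estimate.

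Finally, feasibility is the primary objective, and the Discussion concedes low power and limited comparability with usual care. This limits the severity.

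**Conclusion.** The point holds conditionally. If default variance is used, the consequence is material for complications analysed as yes/no at about 50%: intervals about 41% too wide with equal risks, or about 26% at 50% versus 25%. It is minor at 10-15% (about 5-8%) and negligible at 4% (about 2%). If counts are analysed, coverage falls from 95% to between about 92% and 74% over the assumed dispersion range of 1.25 to 3, with no loss when the variance equals the mean. The 50% versus 25% figure rests on groups of up to 100 and 50; the equal-risk width ratios do not depend on group size.

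The mismatch between morbidity and mortality is visible in the text and needs no assumption. Both matters concern exploratory analyses with no decision rule attached, so this is a worthwhile correction of moderate severity and not a condition for running the trial.

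**What to change.** 1. State for each event outcome, at 30 and 90 days, whether it is analysed as a patient-level yes/no variable or as a count.
2. Use robust (sandwich) variance with the Poisson model in either case, or a negative binomial model for counts. Apply it regardless of outliers, and stop relying on the outlier-triggered bootstrap for these outcomes.
3. Reconcile morbidity in the Analytic Plan with the mortality outcome declared in the abstract. If a slip, correct it; if meant as a separate outcome, define it.
4. Report mortality separately, with an exact interval, because few deaths are expected and one group may have none.

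There is no need to redefine the outcomes as any event or to add a severity cut; the first would discard repeat events and change the quantity estimated from a rate to a risk.

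The cost is a few sentences and a variance option in R, with no extra data collection. Robust intervals came out slightly below nominal for overdispersed counts (93.7% to 94.1% in the simulation), and exact intervals for mortality will be wide. Both are acceptable here.
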